## Abstract

**Introduction:**

Patients recovering from long COVID often endure a spectrum of neuropsychiatric symptoms, including cognitive impairment, memory deficits, mood disturbances and sleep disorders, that significantly impact their quality of life. Acupuncture, particularly electroacupuncture, has shown promise in addressing these symptoms. Currently there is no high-quality clinical trial for acupuncture on long COVID neuropsychiatric symptoms.

**Methods and analysis:**

In this 24 weeks, sham-controlled, patient-assessor-blinded randomized trial, 150 long COVID patients will be equally allocated to either an electroacupuncture group (EAG) or a sham control group (SCG). Each subject will receive a total of 32 intervention sessions over a 16 weeks intervention phase (two sessions each week) and will be followed up for an additional 8 weeks. Primary outcomes include changes in the Mini-Mental State Examination (MMSE) and the Chinese version of the Beck Depression Inventory (CBDI) scores. Secondary outcomes include the Insomnia Severity Index (ISI), Brief Fatigue Inventory-Taiwan (BFI-T), and the Short Form 12 (SF-12). All outcomes will be assessed at baseline and then at 4 weeks intervals during both the treatment and post-treatment periods.

**Discussion:**

This trial aims to generate robust clinical data on the therapeutic effects of electroacupuncture for long COVID. The anticipated results will clarify electroacupuncture’s value as a therapeutic option for neuropsychiatric symptoms in long COVID patients, contributing to evidence-based practice in integrative medicine.

## Introduction

Since SARS-CoV-2 first emerged in late 2019, COVID-19 has profoundly disrupted both public health and socioeconomic systems around the globe. Although the World Health Organization (WHO) officially ended the global public health emergency on 5 May 2023, chronic health issues stemming from COVID-19 continue to affect many recovering patients. These lingering symptoms, which emerge 3 months after infection, persist for a minimum of 2 months, and cannot be attributed to alternative diagnoses, are classified by the WHO as post-COVID-19 condition, or long COVID (1). Epidemiological studies from various countries report high prevalence rates of long COVID (2–9), marking it as a pressing public health issue. This condition involves a broad spectrum of multisystem complaints, predominantly severe fatigue, exertion-related malaise, shortness of breath, palpitations, brain fog, and sensory disturbances such as loss of taste or smell (10–14).

Among the various symptoms triggered by long COVID, neuropsychiatric symptoms have garnered significant attention, including cognitive impairment (15–18), persistent fatigue, anxiety, and depression (10–14). The potential mechanisms underlying long COVID remain unclear, with prevailing theories including persistent viral reservoirs (19), persistent inflammation (20), sustained autoimmune responses (21), host microbiome factors (22, 23), and endothelial dysfunction leading to subsequent blood coagulation (24). However, these theories are still in the hypothesis stage, and effective treatments remain lacking. While existing approaches such as cognitive behavioral therapy (CBT) and nasal irrigation provide some symptom relief (25–27), their efficacy is inconsistent and often associated with side effects, highlighting the urgent need to develop safe and effective non-pharmacological therapies to address the potential long-term impacts of long COVID.

Acupuncture, a widely used technique in traditional Chinese medicine (TCM), is commonly applied in the treatment of neurological and neuropsychiatric disorders. Previous studies have shown that acupuncture can regulate central nervous system activity, thereby improving emotional issues such as anxiety and depression (28, 29). Additionally, acupuncture has demonstrated significant efficacy in treating fatigue syndrome and insomnia (30–32). During the pandemic, acupuncture was employed as an adjunctive treatment in China with formal clinical guidelines (33). Collectively, these results imply that acupuncture could serve as a potential therapeutic approach in managing long COVID. Within acupuncture stimulation protocols, both manual needling and electrical stimulation at acupoints are routinely employed (34). And electroacupuncture has shown unique advantages in enhancing neural regulation and mitigating cognitive impairments associated with central nervous system disorders (35, 36). Pei (37) demonstrated that electroacupuncture substantially alleviated deficits in spatial memory. Electroacupuncture can significantly making its intervention in neuropsychiatric symptoms more targeted (38). However, there is currently no electroacupuncture research addressing neuropsychiatric symptoms in long COVID, and high-quality clinical evidence is lacking.

Building on this, the present study employs a prospective, sham-controlled clinical protocol with participants randomly allocated to receive electroacupuncture within a TCM-guided individualized treatment framework, to rigorously assess its therapeutic impact on neuropsychiatric manifestations of long COVID. The innovation of this study lies in its integration of individualized treatment concepts with randomized controlled trial design, aiming to provide a safe and effective non-pharmacological intervention option for long COVID patients and to advance the clinical application of acupuncture in managing neuropsychiatric symptoms in the post-pandemic era.

## Methods and analysis

### Trial design and setting

This is a prospective, patient-assessor-blinded, randomized, sham-controlled, multi-center trial designed to examine electroacupuncture’s impact on neuropsychiatric sequelae in long COVID survivors. A total of 150 eligible participants will be allocated in equal numbers to either the electroacupuncture group (EAG) or the sham control group (SCG). Each cohort will complete 32 intervention sessions over a 16 weeks period (2 sessions weekly) and will be followed up for an additional 8 weeks. The primary outcomes will be the changes in the Mini-Mental State Examination (MMSE) and the Chinese Beck Depression Inventory (CBDI) scores before and after treatment. Secondary outcomes will include changes in the Insomnia Severity Index (ISI), Brief Fatigue Inventory-Taiwanese (BFI-T), and the 12-item Short-Form Health Survey (SF-12) scores during the treatment and follow-up periods. These questionnaires (Appendix 1) will be assessed every 4 weeks during both the treatment and follow-up periods. The schedule detailing participant enrolment, intervention administration and outcome assessments are summarized in Table 1, while a flow diagram of the trial design is presented in Figure 1. This trial has been registered in clinicaltrials.gov (NCT05890508) and approved by the Research Ethics Committee of Hong Kong Baptist University (REC/21-22/0467).

**TABLE 1 T1:** Schedule for outcome measurement.

Period	B	T																F	
**Visit**	**1**				**2**				**3**				**4**				**5**	**6**	**7**
**Week**	**0**	**1**	**2**	**3**	**4**	**5**	**6**	**7**	**8**	**9**	**1** **0**	**1** **1**	**1** **2**	**1** **3**	**1** **4**	**1** **5**	**1** **6**	**2** **0**	**2** **4**
General assessment	√																		
Screening for enrolment	√																		
Treatment (acupuncture/sham-acupuncture)	Twice a week (16 week treatment)																		
MMSE	√				√				√				√				√	√	√
CBDI	√				√				√				√				√	√	√
ISI	√				√				√				√				√	√	√
SF12	√				√				√				√				√	√	√
Adverse event report	As needed																		

B, baseline; T, treatment phase; F, follow-up phase; MMSE, Mini-Mental State Examination; CBDI, Chinese Beck Depression Inventory Fast Screen; ISI, Insomnia Severity Index; SF12, the Short Form 12.

**FIGURE 1 F1:**
[figure not shown]
Trial design flow chart.

### Sample size

The target sample size was determined by reviewing prior trials using MMSE and BDI to assess the effectiveness of acupuncture versus sham treatment. The observed differences in MMSE and BDI scores between groups were 2.82 and 3.96 points, respectively (39, 40). Based on effect sizes of 0.76 for MMSE and 0.75 for BDI, the BDI-based between-group difference was smaller and was therefore selected for estimation of sample size to yield a more conservative result. To control the overall type I error and ensure sufficient statistical power, the following parameters were applied: a two-sided α level of 0.025 (Bonferroni correction), a power of 0.8, and an equal allocation ratio (1:1) between the acupuncture and sham acupuncture groups. Under these assumptions, the calculation yielded a requirement of 36 subjects per arm. Allowing for an anticipated 20% dropout rate, the target total sample size was adjusted to 90 cases. To increase robustness and ensure an adequate sample reserve for future subgroup analyses, we plan to recruit 150 participants (41–44). Sample size estimation was conducted using G*Power (Version 3.1).

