### Data processing and analysis

Descriptive metrics, namely recruitment rates, attrition rates, and treatment adherence, will be reported as count and percentage. All efficacy and safety endpoints will be analyzed under a modified intention-to-treat (ITT) framework. Statistical analyses will be conducted using SPSS for Windows (version 27.0). Statistical significance is defined as a two- sided *P*-value < 0.05. Baseline continuous variables will be expressed as mean ± SD (or median and interquartile range, as appropriate), and categorical variables as frequencies and percentages. Between-group comparisons of normally distributed continuous outcomes will use independent-samples *t*-test, while non-parametric continuous variables will be assessed with Mann-Whitney U test. Categorical data will be evaluated using chi-squared test or Fisher’s exact test. Group differences at weeks 16 and 24 will be tested via analysis of covariance (ANCOVA), adjusting for baseline values. Within-group changes over time will be examined with pair *t*-test for parametric data and Wilcoxon signed-rank test for non-parametric data. Based on the ITT, missing efficacy data will be imputed by last observation carried forward.

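### Testing MMSE and CBDI by Holm instead of single-step Bonferroni would keep the 5% family-wise error and gain some power at no cost in patients; the gain is modest at the planned effects

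*Protocol article*

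**What the plan says.** The Trial design and setting section names two primary outcomes: "The primary outcomes will be the changes in the Mini-Mental State Examination (MMSE) and the Chinese Beck Depression Inventory (CBDI"), measured before and after treatment. The Sample size section states the aim of controlling the overall type I error and does so with a two-sided "level of 0.025 (Bonferroni correction), a power of 0.8, and an equal allocation ratio (1:1"). No other multiplicity method is named in the document.

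The calculation uses standardised effects: "Based on effect sizes of 0.76 for MMSE and 0.75 for BDI". It takes the smaller one, reaches 36 per arm, allows 20% dropout to reach 90 in total, and then raises recruitment to 150.

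The Data processing and analysis section does not repeat the split. It says: "Statistical significance is defined as a two- sided *P*-value < 0.05". It tests group differences by ANCOVA adjusted for baseline at both week 16 and week 24.

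**The concern.** For two hypotheses, single-step Bonferroni tests each at 0.025 whatever the other shows. Holm tests the smaller P at 0.025 and, only if that succeeds, tests the other at 0.05. Both procedures hold the family-wise error at 5% under any correlation, and Holm rejects everything Bonferroni rejects, sometimes more.

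If the plan is carried through as single-step Bonferroni, a second primary outcome with P between 0.025 and 0.05 could not be claimed even when the first is clearly positive. What is at stake is power on each outcome, and above all the chance of a confirmed result on both cognition and mood. The validity of the trial is not at stake.

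**Working it through.** **Inputs from the Sample size section.** Effects d = 0.76 (MMSE) and 0.75 (BDI), two-sided alpha 0.025, power 0.80, 1:1 allocation, 20% dropout, 150 recruited. Evaluable per arm: 75 × 0.8 = 60.

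**Assumptions not in the documents.** Correlation between the two test statistics of 0 to 0.5, and the smaller effects used in step 4.

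**1. The plan's own figure.** Two-sample t-test, noncentral t, noncentrality d√(n/2), 2n − 2 degrees of freedom. At d = 0.75 and alpha 0.025, power is 79.9% with 35 per arm and 81.1% with 36. So 36 per arm is right, and 72 / 0.8 = 90 is right.

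**2. Family-wise error of Holm.**
- If both null hypotheses hold, an error requires the smaller P to be below 0.025. The chance is at most 2 × 0.025 = 5% (1 − 0.975² = 4.9% if independent).
- If only one null holds, an error requires that P to be below 0.05, so again at most 5%. Bonferroni uses only 2.5% here.

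**3. Power at the plan's effects.** Write a for power at 0.025 and b for power at 0.05. With independent tests:
- Holm power for outcome 1 = a₁ + (b₁ − a₁)a₂.
- Holm power for both = a₁a₂ + (b₁ − a₁)a₂ + (b₂ − a₂)a₁.

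At 36 per arm, MMSE has a = 0.8225 and b = 0.8887; CBDI has a = 0.8114 and b = 0.8806.
- CBDI: 0.8114 + 0.0692 × 0.8225 = 0.868.
- Both: 0.667 under Bonferroni; 0.667 + 0.057 + 0.054 = 0.778 under Holm.

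At 60 per arm, MMSE has a = 0.9697 and b = 0.9849; CBDI has a = 0.9658 and b = 0.9828.
- CBDI: 0.9658 + 0.0170 × 0.9697 = 0.982.
- Both: 0.9365 under Bonferroni; 0.9365 + 0.0165 + 0.0147 = 0.968 under Holm.

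**4. Smaller or unequal effects at 60 per arm (assumed).**
- d = 0.50 on each: a = 0.680, b = 0.775. Per outcome 0.680 + 0.095 × 0.680 = 0.745. Both: 0.463 under Bonferroni; 0.463 + 2 × 0.095 × 0.680 = 0.592 under Holm.
- d = 0.75 and 0.40: the weaker outcome has a = 0.471 and b = 0.584, giving 0.471 + 0.114 × 0.966 = 0.581.

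**5. Effect of correlation.** Simulated pairs of t statistics, 300,000 per setting, correlation 0, 0.3 and 0.5:

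| Setting | Quantity | Bonferroni | Holm |
|---|---|---|---|
| 36 per arm, 0.76/0.75 | CBDI | 81% | 86–87% |
| | both | 67–71% | 78–80% |
| 60 per arm, 0.76/0.75 | CBDI | 97% | 98% |
| | both | 94% | 97% |
| 60 per arm, 0.50/0.50 | each | 68% | 74% |
| | both | 46–53% | 59–64% |
| 60 per arm, 0.75/0.40 | weaker outcome | 47% | 58% |

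Power for at least one outcome is the same under both rules in every setting.

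**6. The analysis section read literally.** Two independent tests at 0.05 each give a family-wise error of 1 − 0.95² = 9.75%. If weeks 16 and 24 are both confirmatory there are four tests. Even at 0.025 each, four independent tests give 1 − 0.975⁴ = 9.6%. A two-outcome Holm rule therefore holds 5% only with one named time point.

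**The case against.** The strongest reply is that nothing in the Sample size sentence is wrong. Bonferroni is valid, the number per arm is correct, and the remedy leaves that sentence untouched. Preferring one valid procedure to another is an efficiency suggestion. That stands, and it sets the priority.

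A reader might also infer that the plan will call a second outcome with P between 0.025 and 0.05 negative. The document does not say so. The split appears only as a sample-size parameter, and the analysis section's P < 0.05 would, read literally, count that result as significant. The loss arises only once the two sections are reconciled to single-step 0.025. But reading 0.05 for each outcome abandons the 5% overall error that the Sample size section sets out to control. A rule has to be written in any case, and Holm is the better one to write.

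A reader might infer that the trial must win on both outcomes, since the largest gains are there. No section makes both a condition of success or powers for it. The gains for both describe a possible aim, not a stated one.

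On size, the large gains at 60 per arm need effects smaller than the plan's, and the document gives none. Some support for considering them is that the eligibility table requires only one neurological symptom and sets no minimum impairment on MMSE or CBDI, so room to improve may differ between the scales. Finally, the powers above are for unadjusted t-tests. Where baseline predicts outcome, ANCOVA has higher power, and at the planned effects the gain would be smaller still.

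An unseen analysis plan may already contain a step-down rule. That would be compatible with sizing at 0.025 and would settle the point.

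**Conclusion.** The point holds as a cheap improvement, optional in priority. Single-step Bonferroni is valid and the sample size is right, but Holm is at least as powerful at the same 5% family-wise error.

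At the plan's effects with 60 evaluable per arm, the gain is about 1 to 2 percentage points per outcome and about 3 for both. It reaches about 6 points per outcome with an assumed effect of 0.50 on each, and about 11 points on the weaker outcome with assumed effects of 0.75 and 0.40. The chance of at least one positive primary outcome does not change.

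These figures rest on a correlation of 0 to 0.5, on 20% dropout, and on unadjusted tests. They do not show that the trial is underpowered or its sample size wrong.

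**What to change.** - **Sample size:** keep 0.025 as the conservative planning level. The number per arm does not change.
- **Data processing and analysis:** for the two primary outcomes, replace the unadjusted P < 0.05 with Holm, applied to the baseline-adjusted ANCOVA P values for MMSE and CBDI at one named primary time point. Week 16, the end of treatment, fits the definition of the primary outcomes as change across treatment. Test the smaller P at 0.025 two-sided; if it is significant, test the other at 0.05; if not, stop. Treat week 24 as secondary.
- **Reporting:** intervals matched to Holm are less simple, so give 97.5% intervals alongside.

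The cost is a sentence or two of text and no extra patients. The rule must be fixed before unblinding, because chosen later it would be post hoc. The same text also removes the disagreement between the two sections on the primary significance level.

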### Randomization and blinding

Participants will be randomized in a 1:1 ratio to either the EAG or SCG. Those allocated to the active treatment arm will undergo standardized electroacupuncture sessions, while the control arm will receive an equivalent sham procedure. A computer-generated simple randomization sequence will be created prior to the study, without stratification or block assignment. The randomization procedure will be conducted by the research unit of the School of Chinese Medicine, Hong Kong Baptist University. Allocation codes will be placed in sequentially numbered, opaque, tamper-evident envelopes and stored in a locked cabinet, with sole key custody maintained by the Principal Investigator (PI). All participants, outcome assessors, statisticians, and all research staff involved in patient contact-except the acupuncturists delivering the treatments, will remain blinded to treatment assignment. To assess the success of blinding, the James Blinding Index will be used at the end of the study. Emergency unblinding is allowed if serious adverse events arise and immediate measures are required to ensure participant safety. Any request for emergency unblinding must be submitted to the PI by co-investigator. Appropriate medical interventions will be provided promptly, and the reasons for unblinding will be documented in detail, including the date and signature of the responsible investigator. The participant involved will be withdrawn from the study.

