### Participants

Participants will be enrolled through two primary channels: (1) newspaper advertisements inviting interested individuals to contact the research team via telephone; or (2) referrals from clinics affiliated with the Hong Kong Hospital Authority. The relevant clinical teams will first contact potential participants, after which the research staff will conduct eligibility screenings. During the initial consultation, a physician (co-investigator) will conduct a detailed clinical history review and comprehensive examination. the PI or a designated co-investigator will furnish potential participants with detailed information regarding the study objectives, methodology, and any risks associated with acupuncture. Written informed consent (Appendix 2: Participant Consent Form) will be obtained prior to participation. Participants will also be informed of their right to withdraw at any point during the study. A total of 150 long COVID patients with neuropsychiatric symptoms will be recruited. The study will be conducted across six Chinese Medicine Research and Clinical Centers of Hong Kong Baptist University. Eligibility criteria are detailed in Table 2.

**TABLE 2 T2:** Inclusion and exclusion criteria.

Inclusion criteria	Exclusion criteria
• Aged 18–80 years.**** • History of SARS-CoV-2 PCR + at least 4 weeks prior; PCR-negative at study entry.**** • At least one persistent neurological symptom (e.g., impaired concentration, headache, sensory disturbances, depression, or “brain fog”) starting around acute COVID-19.**** • Able and willing to consent and complete all assessments and procedures.	• Chronic/remote neurological disorders (e.g., stroke, head trauma, epilepsy, tumor). • Pre-existing intellectual disability. • Cardiovascular diseases (e.g., arrhythmia, heart failure, myocardial infarction, pacemakers). • Acute brain injury or encephalopathy from non-COVID causes (e.g., sepsis, organ failure, drug toxicity). • Documented pre-existing psychiatric illness, including substance abuse. • Open-heart surgery or cardiac arrest within the last 6 months. • Current hospitalization. • Pregnancy.

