## Discussion

This work outlines a single-center, parallel-group trial employing randomization and sham control to rigorously assess the safety and therapeutic efficacy of electroacupuncture for neuropsychiatric manifestations of long COVID. The trial employs strict randomization and blinding procedures to ensure scientific rigor and reliability. The primary and secondary outcomes were chosen to assess multiple dimensions, including cognition, emotion, sleep, and fatigue, allowing for a comprehensive evaluation of the intervention’s potential benefits.

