### Potential limitations

This trial has certain limitations. First, the treatment schedule and frequency might pose challenges to patient adherence. Second, as a single-center study, the characteristics of participants may reflect only the local population, limiting external generalizability. Additionally, the sham stimulation may not fully eliminate psychological effects, requiring careful consideration during data analysis.

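### Simple randomization in a six-centre trial very probably will not give the equal arms the protocol states, and neither the allocation nor the stated ANCOVA accounts for centre

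*Protocol article*

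**What the plan says.** Four statements in the protocol article bear on this point.

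- **Arm sizes.** Trial design and setting: "150 eligible participants will be allocated in equal numbers to either the electroacupuncture group (EAG) or the sham control group (SCG"). The abstract says the same in other words.
- **Allocation method.** Randomization and blinding first gives the ratio, "Participants will be randomized in a 1:1 ratio to either the EAG or SCG", and then the mechanism: "A computer-generated simple randomization sequence will be created prior to the study, without stratification or block assignment".
- **Centres.** Participants: "The study will be conducted across six Chinese Medicine Research and Clinical Centers of Hong Kong Baptist University". Trial design and setting also calls the trial multi-center. The Discussion opens differently, "This work outlines a single-center, parallel-group trial", and Potential limitations says "as a single-center study, the characteristics of participants may reflect only the local population".
- **Analysis.** Data processing and analysis tests group differences at weeks 16 and 24 by ANCOVA with the baseline value as the only named covariate. Centre is not mentioned.

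The sizes of the six centres are not given.

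**The concern.** Equal arms and simple randomization are different promises. A 1:1 ratio under simple randomization is a probability for each participant, and the realised arm sizes are random. Equal numbers need a restriction such as blocks, and the protocol expressly rules that out. As written, the stated method does not deliver a stated property.

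The same choice leaves the balance within each centre to chance. In a trial of six sites, centre is the usual first candidate for stratification, and a centre term in the model is the usual companion. Here the first is excluded and the second is not named. At stake are a little precision and how easily the result can be read if one or two centres turn out lopsided. The single-center statements add to the difficulty, because whether centre needs handling at all depends on which description is correct.

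**Working it through.** **1. The protocol's own sample size.** Inputs from the Sample size section: standardized effect 0.75, two-sided alpha 0.025, power 0.80, ratio 1:1. The two-sample t-test with the noncentral t distribution gives power 0.799 at 35 per arm and 0.811 at 36 per arm, so 36 per arm is reproduced. With 20% dropout, 72 / (1 − 0.20) = 90, also reproduced. The planned total is 150.

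**2. Arm sizes overall.** Under simple randomization the size of one arm is Binomial(150, 0.5), with SD √(150 × 0.25) = 6.1.

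| Event | Probability |
|---|---|
| Exactly 75:75 | 6.5% |
| Arms differ by 10 or more (80:70 or worse) | 46% |
| Arms differ by 20 or more (85:65 or worse) | 12% |
| Arms differ by 30 or more (90:60 or worse) | 1.8% |

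The range 63:87 to 87:63 covers 96% of allocations.

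**3. What unequal arms cost.** Relative efficiency is 4 × n1 × n2 / N². For 63:87 it is 4 × 63 × 87 / 150² = 0.974. After 20% loss, 75:75 becomes 60:60 and 63:87 becomes 50:70. Power at effect 0.75 and alpha 0.025 is then 96.6% and 96.1%. Overall imbalance is immaterial to power.

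**4. Balance within a centre.** Centre sizes are not given, so a range is shown. The event is 68% or more of a centre's participants in one arm, under Binomial(n, 0.5), two-sided.

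| Participants in the centre (assumed) | Split or worse | Probability |
|---|---|---|
| 10 | 7:3 | 34% |
| 25 | 17:8 | 11% |
| 40 | 28:12 | 1.7% |

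If all six centres had 25 (150 / 6), at least one would reach 17:8 or worse with probability 1 − (1 − 0.108)⁶ = 50%. That figure depends on the assumed size.

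**5. Consequence for the treatment comparison.** Null simulation, 20,000 runs per setting, six centres of 25, outcome variance 1, analysed without centre, nominal alpha 0.025. The centre intraclass correlations (ICC) are assumptions.

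| ICC | SE, simple | SE, centre-stratified | Type I error, simple | Type I error, stratified |
|---|---|---|---|---|
| 0 | 0.163 | 0.163 | 0.024 | 0.026 |
| 0.05 | 0.164 | 0.159 | 0.025 | 0.021 |
| 0.10 | 0.162 | 0.155 | 0.024 | 0.019 |

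The mean difference was about 0 in every setting. At ICC 0.10 the ratio of SEs is 0.162 / 0.155, about 4% larger under simple randomization. The last column shows why stratification and a centre term belong together: stratified allocation analysed without centre is conservative and wastes the gain.

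**6. Keeping simple randomization but adding centre.** With centre in the model, the information on treatment is the sum over centres of n1 × n2 / n. Under simple randomization its expectation is 6 × (25/4) × (24/25) = 36. At ICC 0.10 the SE is about √(0.90 / 36) = 0.158, between 0.162 (simple, no centre term) and 0.155 (stratified). At ICC 0 it is about √(1 / 36) = 0.167 against 0.163, a small price if centres do not differ.

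**The case against.** The strongest case on the other side is that simple randomization with sequentially numbered, opaque, tamper-evident envelopes is fully valid and the least predictable scheme available. That matters here: the acupuncturists are unblinded, and the principal investigator alone holds the key to the envelopes and may also brief potential participants. The protocol needs 36 evaluable per arm, or 45 before dropout, and with 150 randomized neither arm will realistically fall short. On this view the equal-numbers statement needs only a change of wording. A centre covariate could be in an analysis plan that is not shown, and the single-center phrase is a separate drafting slip.

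Much of this stands. The effect on power is negligible, and the missing centre term would not be a finding by itself, since the article does not exclude one. Two things do not fall away. An analysis plan can add a covariate but cannot change an allocation method that the protocol has fixed. And predictability is largely met by block sizes that vary at random and are not disclosed, together with the envelopes already planned.

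A reader might go further and infer that centre is confounded with treatment. It is not: imbalance that arises by chance under valid concealed randomization causes no bias in expectation, and the simulated type I error stayed at 0.024 to 0.025. Nor can one infer confounding by practitioner, assessor or referral route. The article gives practitioner qualifications and two recruitment channels for the trial as a whole, but not how many practitioners or assessors there are or how any of these differ between centres.

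**Conclusion.** The point holds as an inconsistency and an avoidable inefficiency, not as a threat to validity. The stated method yields the stated equal arms with probability 6.5%, which needs no assumption beyond simple 1:1 randomization of 150. Centre is handled neither in the allocation nor in the analysis as described, and the document contradicts itself on whether there is one centre or six.

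The cost is small: nothing in bias or type I error, about half a percentage point of power (96.6% to 96.1%) at 63:87, and a standard error about 4% larger at an ICC of 0.10, falling to nil at 0. The precision figure rests on assumed ICCs and six equal centres; the within-centre imbalance figures rest on assumed centre sizes. The change is worth making because it is standard and cheap, not because the primary results would otherwise be unsound.

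**What to change.** Preferred, if enrolment has not begun: generate the list in permuted blocks of randomly varying, undisclosed size, stratified by centre, and add centre as a term in the ANCOVA at weeks 16 and 24. With small blocks this keeps the arms near 75:75, and a centre of 25 near 12:13.

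If enrolment has begun, or the sponsor prefers simple randomization: replace the equal-numbers wording in the abstract and in Trial design and setting with a 1:1 allocation probability, and add centre to the ANCOVA. This avoids a change of allocation method part-way through.

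In either case, reconcile the single-center wording in the Discussion and Potential limitations with the six centres named under Participants.

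Cost: a new computer-generated list, a separate envelope series for each centre with the custody that goes with it, one model term and a few wording changes. The downside of blocking is slight predictability at block ends, limited by varying and concealing the block sizes. The centre term costs a little precision if centres do not differ.
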